Stakeholders need support to implement the guidelines in their school (15, 26, 27). Such an implementation support plan will be better aligned to the needs of practice, and thereby more feasible, if the needs and wishes of stakeholders are taken into account (9, 28, 29). Therefore, during the development and evaluation stage, collaboration with these stakeholders is recommended (28, 29). It is also recommended to apply theory, such as the use of a structural framework for the development and evaluation of the implementation plan, the use of behavior change models to translate the need of practice into implementation strategies and the use of a combination of implementation tools (30, 31). The collaboration with practice in combination with the use of theory will increase the likelihood of a feasible and effective implementation. To succeed over time, implementation of new guidelines should allow adaptations to local circumstances but, nonetheless, be conducted with rigor and consistency. This article describes: (1) how we developed a plan to support implementation of canteen guidelines in Dutch secondary schools; and (2) how we will evaluate this implementation plan on process and effect level. The process will be evaluated on factors affecting implementation perceived by stakeholders and the quality of implementation. The effect will be evaluated by determining changes in the health level of canteens and in the self-reported purchase behavior of adolescents.

The input of practice during the development and evaluation of our implementation plan will give insights to researchers about working elements. We hypothesize that this approach will increase future uptake and effect of the implementation plan. With our implementation plan we aim to facilitate the process to create a healthier school canteen, and thereby to stimulate Dutch adolescents to purchase healthier foods and beverages during school time.

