### Evaluation of the Implementation Plan on Process and Effect Level

#### Setting and Study Design

To evaluate both the process and effect of the developed implementation plan, a 6-month quasi-experimental controlled design will be used with 10 intervention and 10 matched control schools (see Figure 2). The included schools will have a variety of characteristics, so the results can be translated to other Dutch schools. Control schools will be matched by the main characteristics: how the catering is provided (i.e., by a catering company, or the school itself), school size (<1,000 and ≥1,000 students), level of secondary education (vocational, senior general, and pre-university), availability of (many) shops near the school, and whether or not the school has a policy for students to stay on the schoolyard during breaks. Intervention schools will receive the developed implementation plan to support implementation of the Guidelines for Healthier Canteens, whereas the control schools will receive the guidelines only. Control schools will receive these guidelines in a short meeting and on paper after the baseline measurements. After the intervention period, control schools will receive the intervention. This quasi-experimental study will be carried out according to: (1) the project application (Nr: 50-53100-98-043, date: 2 December 2014) approved by funding organization ZonMw, (2) the study protocol approved by the VU University Medical Centre (WC2015-008 and 2015.331), and (3) registration in the Dutch Trial Register (NTR5922).

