**Canteen Scan (measured at T0 and T2)**			
Health level of the canteen (availability and accessibility of healthier food and drinks)	Multiple choice	Basic conditions for all canteens	Encourages the school canteen people to drink water? (i.e., by water tap)
	Open Question	Percentage of available healthier food and drinks on display	Please enter all products on display (at the counter, in display cases and on racks) in the school canteen
	Open Question	Percentage of available healthier food and drinks in vending machines	Please enter all products in the vending machine
	Multiple choice	The canteen's accessibility criteria (to motivate people to select a healthier option)	Does the school canteen present fruit or vegetables in an attractive manner?

a *Asked for each implementation component*.

b *Only measured at T2*.

c *Only measured by the stakeholders of the intervention schools*.

d *Also measured by logging the use digital*.

The second process evaluation outcome is the quality of implementation. After 6 months, all stakeholders in the intervention group will be asked to evaluate the quality of each implementation tool. With an online questionnaire, quantitative process evaluation measures derived from the methodology of Saunders et al. (43) and Steckler and Linnan (44) will be measured. Fidelity will be measured with dose delivered and dose received. In addition, satisfaction will be measured. *Dose delivered:* Number of stakeholders to whom the tool was provided by the school canteen advisors. *Dose received:* Number of stakeholders who received and used the tool. *Satisfaction:* Participant's satisfaction with each tool. Additionally, objective data collection will be conducted by digitally logging the delivery and use of each online implementation tool. Moreover, after the intervention via open-ended questions in the questionnaire and during an evaluation meeting, all stakeholders will be asked to: explain their satisfaction score; give a short evaluation per implementation tool; give their positive and negative experiences overall; and to give their suggestions for improvements (qualitative data).

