The secondary outcome “health level” of the school canteen will be measured with the online tool, “the Canteen Scan.” This tool was developed and improved and improved in an iterative process through a collaboration of researchers, professionals, schools, caterers, and experts on nutrition and health behavior, and tested on its validity and inter-rated reliability (42, 52). The Canteen Scan checks to what extent a canteen meets the Guidelines for Healthier Canteens and subsequently provides tailored advice for improvements. The three parts of the guidelines can be entered in this tool: (1) a set of basic conditions for all canteens, (2) the food and drink available on display and in vending machines, and (3) the accessibility of healthier food and drink products (21, 42). Subsequently, the school canteen's current overall level (silver or gold), and a level for all three individual parts (in percentages) is indicated. Consequently, the health level of the canteen can be defined as: the available basic conditions, the available healthier food and drinks and meeting the accessibility criteria in the school canteen. The Canteen Scan will be filled out in all intervention and control schools by a school canteen advisor. Intervention schools will receive the outcome and feedback as part of the intervention. On the contrary, the control schools will not receive the results or feedback from the Canteen Scan.

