##### Effect evaluation

After the intervention, differences in the primary outcome “purchase behavior” of students (dependent variable) between the intervention and control group (independent variable) will be analyzed with two-level regression analysis (intention-to-treat). Here, we will correct for correlations of students (level 1) nested within schools (level 2). We will adjust for confounders related to students (e.g., groups of sociodemographic characteristics, behavioral determinants, and environmental determinants). In addition, the moderation effect of gender will be taken into account by stratifying the analyses, based on literature (56). We hypothesize that students in the intervention group will achieve a healthier purchase behavior.

After the intervention period, differences in the secondary outcome “health level” of the canteen between the intervention and control schools will be investigated with descriptive statistics. Thereafter, to gain insight into the effect of the health level of canteens and purchase behavior of students, we will include the health level of canteens in a per protocol analysis. This model will be built similar as the explained intention-to-treat analysis. All information is being gathered with rigor, so these analyses will show which factors make a difference in student behaviors, including implementation features. We hypothesize that intervention schools will improve their health level of the canteen, and that a healthier canteen will lead to healthier purchases. Statistical analyses will be performed using the IBM SPSS statistics version 24.0. MLwiN 2.36 software will be used to conduct the multilevel regression analyses. For all statistical analyses, a two-tailed and 5% significance level will be applied (53).

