## Discussion

This study design describes how we developed and will evaluate a plan to implement guidelines to create healthier canteens in secondary schools using a systematic theory and practice-based approach. The study aims to contribute to a feasible and effective implementation of healthier school canteen policy in secondary schools. We hypothesize that schools which will receive support to implement the guidelines, will offer healthier food and beverages and that these products will be more easily accessible in the canteens compared to schools that will not receive support. In addition, we hypothesize that this will be associated with healthier purchase behavior of students in intervention schools.

Implementation of policy to limit the availability of less healthy food in schools is recommended (18) and seems effective (26). However, it also faces challenges, like conflicts with time demands for other school activities, different interests of the stakeholders (e.g., financial profit vs. healthiness), or that the implementation materials will not be used as intended. These challenges may influence the feasibility and the effectiveness of the implementation process. Although these challenges will always be present, the involvement of stakeholders during the development phase and the combination with evidence-based knowledge, frameworks and behavior change methods will result in a plan that effectively intervenes on identified challenges (28, 31). Also, the proper process evaluation will inform us about the extent of these issues. Based on all knowledge this research creates, we are able to further improve the implementation plan.

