This study provides an example how the identified needs of stakeholders can be combined with evidence-based theory to develop an implementation plan. This study will show the impact of implementing guidelines to create healthier canteens in Dutch secondary schools, with support of the developed implementation plan, on the canteen's health level and on the purchase behavior of students. Also, the evaluation will show the appreciation, use and recommendations of the implementation tools, according to stakeholders involved in the process of creating a healthier canteen. These insights will be used to improve the existing school canteen program by supporting stakeholders to create a healthier school canteen.

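### Canteen health level carries a directional hypothesis and a promised impact conclusion, but the only stated comparison between arms is descriptive, with no baseline-adjusted estimate or measure of uncertainty

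*Protocol article*

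**What the plan says.** All references are to the protocol article; no statistical analysis plan is at hand.

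- **Aim (Introduction).** "The effect will be evaluated by determining changes in the health level of canteens and in the self-reported purchase behavior of adolescents". Health level is thus one of two effect outcomes.
- **Hypothesis (Statistical Analysis, Effect evaluation).** "We hypothesize that intervention schools will improve their health level of the canteen, and that a healthier canteen will lead to healthier purchases".
- **Comparative form (Discussion, opening).** Schools given support "will offer healthier food and beverages and that these products will be more easily accessible in the canteens compared to schools that will not receive" it.
- **Promised conclusion (Discussion, closing).** "This study will show the impact of implementing guidelines to create healthier canteens in Dutch secondary schools", with the canteen's health level named as one of the things affected.
- **Design (Setting and Study Design).** "a 6-month quasi-experimental controlled design will be used with 10 intervention and 10 matched control schools".
- **Measurement (Table 2; Outcomes, Effect evaluation).** The table heading reads "Canteen Scan (measured at T0 and T2", and "The Canteen Scan will be filled out in all intervention and control schools by a school canteen advisor". The tool returns an overall level (silver or gold) and a percentage for each of its three parts.
- **Analysis (Statistical Analysis, Effect evaluation).** Once the intervention period is over, differences in health level "between the intervention and control schools will be investigated with descriptive statistics". Health level then enters a per-protocol model as an explanatory variable for student purchases.

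**The concern.** The reasoning of the trial runs from support, to a healthier canteen, to healthier purchases. Health level is the first link and the outcome on which the tools act most directly. The article makes a directional claim about it, yet states no analysis that yields an effect of arm with its uncertainty.

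Two rival explanations for any observed gap are left open. One is chance, with only 20 units. The other is starting level: allocation was not random, and the matching characteristics (catering provision, school size, education level, nearby shops, schoolyard policy) do not include baseline health level. The report could therefore claim an impact that the analysis does not support, or miss a real gain hidden by a poorer start in the intervention schools.

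**Working it through.** **1. Does another stated analysis fill the gap?** The regressions under Statistical Analysis have these dependent variables:

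| Analysis | Dependent variable | Baseline-adjusted |
|---|---|---|
| Process, two-level linear | Stakeholder factors | Yes, stated |
| Effect, intention-to-treat | Student purchases | Confounders named |
| Effect, per protocol | Student purchases, with health level as explanatory variable | Built like the one above |
| Health level between arms | None (descriptive) | Not stated |

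None estimates the effect of arm on health level. The section's general two-sided 5% rule has no test of this outcome to apply to. The process measures get a baseline-adjusted model while the secondary effect outcome does not.

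**2. Is the adjusted analysis possible with the planned data?** Yes. The scan is made at both time points in all 20 schools and gives percentages.

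**3. What precision would it have?** The article gives no sample size, power or SD for this outcome, so there is no figure of its own to reproduce. Inputs: 10 schools per arm, two-sided 5% (both from the article); 80% power (the level the article uses for its primary outcome). The correlation r between the baseline and follow-up percentage is an assumption. Matching is ignored.

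Detectable difference in SD units ≈ (t₀.₉₇₅ + t₀.₈₀) × √(2/10) × √(1 − r²). The 95% CI half-width is t₀.₉₇₅ × √(2/10) × √(1 − r²). √(2/10) = 0.4472.

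- Unadjusted, 18 df: (2.101 + 0.862) × 0.4472 = 1.325; the noncentral t calculation gives 1.32. Half-width 2.101 × 0.4472 = 0.94.
- r = 0.5, 17 df: (2.110 + 0.863) × 0.4472 × 0.866 = 1.15. Half-width 0.82.
- r = 0.7, 17 df: 2.973 × 0.4472 × 0.714 = 0.95. Half-width 0.67.

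If the between-school SD is assumed to be 10 to 25 percentage points, the detectable difference is about 13 to 33 points unadjusted and 9.5 to 24 points at r = 0.7.

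**4. How much can starting level matter?** Sampling variation alone gives the difference in baseline means a standard error of 0.4472 SD. With equal variances at the two times, a baseline gap of one standard error carries forward as r × 0.4472: 0.22 SD at r = 0.5 and 0.31 SD at r = 0.7, with no intervention effect at all. This illustrates scale only; matching could reduce the gap and non-random selection could widen it.

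**The case against.** The strongest reply is that description is a reasonable choice for a secondary outcome with 20 units in a study sized on students. A test would detect only large differences, and a non-significant result could be misread as no effect. This stands as an argument against relying on a p-value. It does not argue against an interval, which shows the imprecision that a bare pair of means conceals.

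Three stronger readings are tempting, and the document does not support them.

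- *A reader might infer that the trial could say nothing about whether canteens improved.* Values at both time points in all 20 schools will show the observed change in each arm. What is missing is inference about that change.
- *A reader might infer that baseline is ignored and only follow-up values compared.* The phrase about the end of the intervention period can simply say when the comparison is made; the primary outcome is introduced almost identically. The Introduction speaks of changes, so a table of baseline, follow-up and change is a natural output. The text supports no stated adjusted estimate, not a disregarded baseline.
- *A reader might infer that intervals are ruled out.* They are neither promised nor excluded.

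The matching, and the exclusion of schools that had already begun the guidelines or been advised in 2015, also make a large imbalance less likely, though neither equalises starting levels.

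An unseen analysis plan might add a model. But the article does not leave the method open: it names descriptive statistics for this outcome.

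**Conclusion.** The concern holds as a mismatch between claim and analysis: a directional, comparative hypothesis and a promised impact conclusion rest on a descriptive comparison with no stated baseline-adjusted estimate or uncertainty. It is of moderate weight, because the outcome is secondary and 20 schools can establish only large differences. Adjustment lowers the detectable difference from about 1.32 SD to 1.15 SD (r = 0.5) or 0.95 SD (r = 0.7), the latter about 28% smaller (1 − 0.95/1.32). Those gains rest wholly on the assumed correlations, which the article does not give; advice aimed at weaker canteens could lower the correlation in the intervention arm. The mismatch itself depends on no assumed figure.

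**What to change.** 1. Keep the descriptive table and state that it shows baseline, follow-up and change by arm, together with the overall silver or gold level.
2. For each Canteen Scan percentage (basic conditions; healthier products available on display; healthier products available in vending machines; accessibility), add a school-level linear regression of the follow-up value on arm with the baseline value as covariate. Report the adjusted difference with a 95% CI, on 17 df when all 20 schools contribute. The inclusion criteria require a canteen but not a vending machine, so that measure may have fewer schools.
3. Present these as secondary estimates, without claims that imply control for multiplicity across the four measures.
4. Add a sensitivity analysis that respects the matching. If schools were matched in pairs, pair terms leave 20 − 12 = 8 df (intercept, nine pair terms, arm, baseline), so its interval may be wider. A permutation check may be added as support only, since schools were not randomised.
5. State that the adjustment deals with measured starting level, not with other differences between non-randomised schools.

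The cost is a few lines of analysis and visibly wide intervals; no new data are needed. If the sponsor keeps description only, the health-level hypothesis and the closing impact statement in the Discussion should be reworded as exploratory.

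### The model labelled per protocol includes a hypothesised mediator, canteen health level, so it gives no per-protocol effect and does not support the causal conclusion drawn from it

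*Protocol article*

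**What the plan says.** All in the protocol article.

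- **Statistical Analysis, Effect evaluation** sets out a two-level intention-to-treat model of purchase behaviour on group, students within schools. On covariates: "We will adjust for confounders related to students". The article then says "we will include the health level of canteens in a per protocol analysis", and on its form: "This model will be built similar as the explained intention-to-treat analysis".
- The same section states the expected chain: "We hypothesize that intervention schools will improve their health level of the canteen, and that a healthier canteen will lead to healthier purchases".
- It draws this conclusion in advance: "these analyses will show which factors make a difference in student behaviors, including implementation features".
- **Outcomes, Effect evaluation** names health level as the secondary outcome. **Table 2** gives its timing: "Canteen Scan (measured at T0 and T2".
- **Setting and Study Design** describes a quasi-experimental comparison of 10 intervention and 10 matched control schools.
- **Statistical Analysis, Process evaluation** gives the tool-level measures (dose delivered, dose received, satisfaction) descriptive statistics, with qualitative data alongside.

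**The concern.** A per-protocol analysis estimates the effect of the intervention when it is delivered or followed as intended. The analysis described here instead brings in a variable that the plan expects the intervention to change and that is expected in turn to change purchasing. That is a mediator model or an association model, and each answers a different question from the one the label suggests.

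Two misreadings are at stake. If group stays in the model, a small group coefficient under a per-protocol heading could be taken to mean that the plan fails when delivered, although the effect has only been reassigned to the health-level term. On either model form, differences between schools that affect both canteen and purchasing could be reported as an effect of the canteen. The sentence promising to show which factors make a difference invites the second misreading.

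**Working it through.** The plan gives no figure on this point, so there is none to reproduce. The check compares the text with itself and then works through the two model forms the text allows.

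**1. Text against text**

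- *Label and content.* The name is per protocol. The content is an intention-to-treat-type model with health level included.
- *Place on the causal path.* Intervention to health level to purchases, by the plan's own hypothesis.
- *Promise and inputs.* The promise covers implementation features, but none is stated to enter the student model. Health level varies by school, yet the confounders named are those of students.

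**2. Two model forms**

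Assumed notation, on school means: *a* is the intervention effect on health level M (in within-arm SDs), *b* the effect of M on purchasing, *c* the direct effect of the intervention. The total effect is c + ab. U is an unmeasured school factor (SD 1) with effect 0.5 on M and 0.5 on purchasing; the within-arm variance of M is held at 1. Take a = 1 and equal arms.

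*M beside group.*
- Coefficient of M = b + (0.5 × 0.5)/1 = b + 0.25 with U, or b without U.
- Coefficient of group = c − a × 0.25 = c − 0.25 with U, or c without U.

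*M in place of group.*
- Var(M) = 1 + a²/4 = 1.25.
- Coefficient of M = b + 0.25/1.25 + c × (a/4)/1.25 = b + 0.20 + 0.20c with U, or b + 0.20c without U.

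| Case | b | c | U | Total effect | Group, M omitted | Group beside M | M beside group | M alone |
|---|---|---|---|---|---|---|---|---|
| 1. Full mediation | 0.5 | 0 | no | 0.50 | 0.50 | 0.00 | 0.50 | 0.50 |
| 2. Full mediation | 0.5 | 0 | yes | 0.50 | 0.50 | −0.25 | 0.75 | 0.70 |
| 3. No effect on purchases | 0 | 0 | yes | 0 | 0 | −0.25 | 0.25 | 0.20 |
| 4. Partial mediation | 0.5 | 0.2 | yes | 0.70 | 0.70 | −0.05 | 0.75 | 0.74 |

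A simulation of 20 schools (4,000 replicates, least squares) agrees with every entry within 0.005. In case 1, the 10% difference used in Sample Size would appear as 0 in the group coefficient if it ran wholly through the canteen.

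**3. Precision (illustrative)**

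- If M stands beside group and the intervention shifts it by d within-arm SDs, the correlation of group with M is r = d/√(d² + 4). The variance of the group coefficient is multiplied by 1/(1 − r²):
  - d = 1: r = 0.447, factor 1.25
  - d = 1.5: r = 0.600, factor 1.56
  - d = 2: r = 0.707, factor 2.0
- Smallest school-level correlation detectable with 80% power at two-sided 5% and 20 schools: tanh(2.80/√17) = tanh(0.679) = 0.59.
- Adjusting for group and the five matching characteristics, counted as one term each: tanh(2.80/√(20 − 3 − 6)) = tanh(0.844) = 0.69.

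**The case against.** The strongest reply is that the mediator problem rests on a model the article does not fully state. It does not say whether health level joins group or replaces it, nor whether the T0 or the T2 scan is used. The wording that places this step after the post-intervention comparison points to T2, but that is an inference. The stated aim concerns the relation of health level to purchasing, which fits replacement as well as addition. If health level replaces group, there is no group coefficient to misread and no variance inflation. This stands, and those consequences are conditional on the model form.

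The label is also not baseless. The Canteen Scan measures how far a canteen meets the guidelines, so health level is a kind of adherence measure. An adherence threshold or per-protocol population can be left to a fuller document, and its absence is not the point here. But health level is also an outcome of the intervention, measured in both arms. Modelling it does not yield the effect of receiving the plan as intended.

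Matching on five school characteristics is relevant too. It balances the arms on those characteristics but does not remove confounding between health level and purchasing across schools.

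A reader might infer that the Discussion repeats the overstatement. It does not: "we hypothesize that this will be associated with healthier purchase behavior of students in intervention schools" is a hypothesis in suitably modest terms. Nor does the Discussion's caution about interpreting tools qualify the Effect evaluation sentence, since it concerns which tools contribute most in the process evaluation.

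**Conclusion.** The point holds on either model form. Beside group, health level changes the meaning of the group coefficient from total effect to what remains after the mediated part is taken out, with expectation 0 under full mediation. In place of group, it gives an observational association across 20 non-randomised schools. Neither is a per-protocol effect, and neither supports the stated conclusion about which factors make a difference. For implementation features the conclusion fails regardless of confounding, because none is stated to enter the student model.

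A reader might go further and infer that the intervention effect will be adjusted away, or that the trial's main result is compromised. The documents do not support this. The intention-to-treat model without health level is the analysis of the primary outcome and is unaffected. Nor does the health-level coefficient have to be wrong: without unmeasured school-level confounding it would be interpretable, but the design does not rule such confounding out.

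The sizes in the working are illustrations. The confounder effects of 0.5 and the 1 to 2 SD shift are assumptions. Health level is reported as an overall level plus three percentages, so a single standardised shift is a simplification. The detectable correlations are school-level approximations to a two-level model. The zero under full mediation also needs a mediator measured without error. This is a correction worth making to a supporting analysis.

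**What to change.** 1. Drop the per-protocol label, and keep the model without health level as the only estimate of the intervention effect.
2. Present the health-level model as an exploratory association analysis, or as a mediation analysis with its assumptions. State the time point and whether group is in the model, and report a confidence interval. Adjust for the school matching characteristics already recorded as far as 20 schools allow. If group is included, say that its coefficient is not to be read as efficacy. Using change from T0 to T2 does not avoid this, since the change is itself on the path.
3. Replace the sentence on showing which factors make a difference with one saying that the analyses will explore associations. Remove the reference to implementation features unless the dose measures are entered in the model.
4. If a per-protocol analysis is wanted, define adherence among intervention schools from the dose-delivered and dose-received measures. Scan completion cannot serve, because advisors complete the scan in all schools. Digital logs alone are not enough, because they cover only the online tools.

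The variables are already collected. The cost is wording, a little analysis and a more modest claim.
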